## 1. Background

Anemia, especially severe anemia, is associated with increased child mortality rates [1]. Moreover, limitations in physical and cognitive development, leading to an increase in academic failure and susceptibility to infectious diseases, are also of great concern [1,2,3,4]. Regional studies conducted in the Dande municipality (Bengo province) reported a 57% prevalence of anemia in under-5 children, indicative of a severe public health problem [5]. In this setting, in addition to the expected association with undernutrition (responsible for nearly 13% of anemia cases), clusters of high risk of anemia were found to overlap with *Plasmodium falciparum* and *Schistosoma haematobium* risk zones (associated with 16% and 10% of the cases, respectively) [5,6].

Around half of anemia cases are estimated to result from Iron Deficiency (ID) [7]. However, in malaria endemic countries, routine iron supplementation remains controversial and is only undertaken with caution, as the practice has been associated with both an increased incidence and severity of malaria, especially in non-iron-deficient anemic people [8,9,10,11,12]. Additionally, single nutrient deficiencies are rare, as insufficient ingestion of other hematopoietic micronutrients may occur and cause nutritional anemia. On the other hand, the high prevalence, intensity, reinfection and incidence rates of anemia-related infections can also contribute to iron deficiency anemia, potentially refractory to iron supplementation [2,5,13,14,15,16].

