## 2. Materials and Methods

### 2.1. Study Setting

This study targets hamlets with functional primary health care facilities within CISA’s Dande HDSS study area [42]. The surveyed area is located in the Bengo Province (Dande municipality), and includes all the hamlets in the communes of Úcua, Caxito, Mabubas, as well as some hamlets in Kikabo and Barra do Dande [42]. Within this area, between 2010 and 2014, the total resident population varied between 63,081 and 58,645, with the percentage of under-5 children ranging from 17.7% to 13.9%. Additionally, the fertility rate varied between 4.8 and 3.7 births per woman, with the crude birth rate ranging from 40.4 to 24.2 live births/year/1000 people and the under-5 mortality rate fluctuating between 92.1 and 60.1 per 1000 live births [42]. As the entire population of Kikabo and Barra do Dande are not fully surveyed by the Dande HDSS, they will not be included in this study. Although 15 hamlets with health facilities are located within this area, only those providing daily primary care practices will be included in this study [43].

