## 3. Cluster-Randomized Controlled Trial

### 3.1. Sampling Strategy

In this study, the sampling strategy chosen was a non-probabilistic (convenient) sampling. In sum, we aimed to include (through a census approach) all eligible children (under the age of 4) resident in administratively and geographically isolated hamlets with functional health posts, in turn located within the CISA’s HDSS study area (considered as cluster units). We chose hamlets with functional health posts due to the greater facility in mobilizing the population and corresponding logistical advantages. On the other hand, the census approach (within those clusters) was adopted because variations in the density of eligible children, estimated according to data from 24-10-2014 extracted from CISA’s HDSS database, was expected, and the real density in each cluster was needed.

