### 3.2. Randomization

The hamlets will be considered as cluster units. For randomization, the names of the hamlets will be written down on pieces of paper and placed in a bag and then successively removed. The first two papers to be removed will be attributed to the Nutrition arm, the following two to the WASH/Malaria arm and the next pair to the control with this procedure repeated until there are no papers left in the bag. This process will be carried out by the two CISA researchers coordinating the study.

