### 5.2. Baseline Assessment Eevaluations

The nutritional quality of children’s diets (24–36 months) will be determined in accordance with the Children’s Individual Dietary Diversity Score Indicator (IDDS) [69,70]. The prevalence of malnutrition in children will be calculated by WHO Anthro software (version 3.2.2). The chi-square test will be used to compare proportions, in addition to calculating the attributable fractions.

Pre-and post-intervention and intervention versus control arms evaluations.

Primary and secondary impact indicators will be evaluated between the baseline and the follow ups (for each study sample), and between the intervention and control arms. Outcomes will be compared analyzing for variance in the continuous variables and logistical regression for the categorical variables. Adequacy and plausibility arguments will be used, by analyzing the process indicators (described in Table 2) in accordance with the conceptual maps. Relative risk will be calculated in order to compare the cumulative incidence of anemia among the intervention and control arms.

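### Hamlets are randomised, but the between-arm analyses named in section 5.2 carry no hamlet term, so their standard errors will be too small if children within a hamlet are correlated

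*Protocol article*

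**What the plan says.** Section 3.2 fixes the unit of allocation: "The hamlets will be considered as cluster units". Names are drawn from a bag in pairs: "The first two papers to be removed will be attributed to the Nutrition arm", the next two go to WASH/Malaria, the next two to control, and the cycle repeats until the bag is empty.

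On the number of units, section 2.1 says: "Although 15 hamlets with health facilities are located within this area, only those providing daily primary care practices will be included in this study". How many pass that screen is not stated. Section 3.1 takes all eligible children in each hamlet and expects "variations in the density of eligible children", so hamlet sizes will be unequal. They are not given.

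The primary outcomes in Table 2, hemoglobin and anemia prevalence, are measured on individual children. For the comparison of arms, section 5.2 states: "Outcomes will be compared analyzing for variance in the continuous variables and logistical regression for the categorical variables". It adds: "Relative risk will be calculated in order to compare the cumulative incidence of anemia among the intervention and control arms".

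The article mentions no hamlet effect, random effect, generalised estimating equations (GEE), cluster-robust error, cluster-level summary, ICC or design effect. The Discussion concedes that outcome frequencies may not even out within clusters. Its answers are kits, provider training, process indicators and plausibility arguments, none of which changes a standard error.

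**The concern.** When hamlets are allocated, the information about an arm comes from how its hamlets differ from those of another arm. An analysis that counts every child as an independent unit takes its error term from variation between children and leaves out variation between hamlets. Chance differences between hamlets can then pass for an effect of education.

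The article gives its own reason to expect such differences. The Background reports that "clusters of high risk of anemia were found to overlap with" malaria and schistosomiasis risk zones. Group delivery of the workshops, and technicians assigned to particular arms, may add further shared variation.

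At stake is the main claim of the trial. An education package could be declared effective against anemia when the hamlets drawn for that arm merely happened to do better.

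**Working it through.** The article gives no sample size, ICC or design effect, so there is no stated figure to reproduce. The check asks how large the error would be under stated assumptions.

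**Inputs**
- Unit of randomisation: hamlet (section 3.2).
- Number of hamlets: at most 15, actual number not stated (section 2.1).
- Anemia prevalence for the simulation: 57% (Background).
- Children per hamlet, m: not stated; assumed 50 to 150.
- ICC: not stated; assumed 0.01 to 0.05.

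**Formulas**, for equal hamlet sizes
- Design effect: DE = 1 + (m − 1) × ICC
- Factor by which the standard error is understated: √DE
- True two-sided error of a nominal 5% child-level test: 2 × [1 − Φ(1.96 / √DE)]

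**Worked case**, m = 100 and ICC = 0.02: DE = 1 + 99 × 0.02 = 2.98. √DE = 1.73. True error = 2 × [1 − Φ(1.96 / 1.73)] = 0.256.

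| m | ICC | DE | SE understated by factor | True type I error |
|---|---|---|---|---|
| 50 | 0.01 | 1.49 | 1.22 | 10.8% |
| 50 | 0.02 | 1.98 | 1.41 | 16.4% |
| 50 | 0.05 | 3.45 | 1.86 | 29.1% |
| 100 | 0.01 | 1.99 | 1.41 | 16.5% |
| 100 | 0.02 | 2.98 | 1.73 | 25.6% |
| 100 | 0.05 | 5.95 | 2.44 | 42.2% |
| 150 | 0.01 | 2.49 | 1.58 | 21.4% |
| 150 | 0.02 | 3.98 | 1.99 | 32.6% |
| 150 | 0.05 | 8.45 | 2.91 | 50.0% |

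Over a wider range (m from 30 to 200, ICC from 0.01 to 0.10), the factor runs from 1.14 to 4.57 and the true error from 8.4% to 66.8%.

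**Simulation.** Beta-binomial data were generated with no treatment effect, 20,000 runs per setting, and 2, 4 or 5 hamlets per arm. At m = 100 and ICC 0.05, the child-level test rejected in 42% to 43% of runs and a t-test on hamlet proportions in 5.1% to 5.5%. Across all settings simulated, the hamlet-level t-test stayed between 4.8% and 5.5%.

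**Degrees of freedom.** With all 15 hamlets, drawing in pairs gives 6, 5 and 4 per arm. A two-arm contrast then has at most 6 + 5 − 2 = 9 df, or 15 − 3 = 12 df (critical t 2.18) if the variance is pooled over three arms. In a scenario of six hamlets, two per arm, a two-arm contrast has 2 df (critical t 4.30), or 6 − 3 = 3 df pooled (critical t 3.18). A 2-versus-2 permutation test has six possible allocations, so its smallest two-sided p is 2/6 = 0.33.

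**The case against.** The strongest reply is that section 5.2 never says that hamlets are ignored. Analysis of variance and logistic regression can both carry a hamlet term, and a journal article commonly leaves model terms to a fuller document. It stands that child-level analysis is inferred. The reply does not remove the point. The article names its methods for a cluster-randomised design, those methods in their usual form assume independence, and nothing elsewhere qualifies them. An analysis plan that followed the text would carry the mismatch forward.

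Several stronger readings are tempting, and the article does not support them:

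- A reader might infer that the standard errors are far too small. That depends on an assumed ICC and hamlet size. At the low end the understatement is modest. Spatial clustering of prevalence also does not give an ICC for change in hemoglobin, where stable hamlet differences cancel.
- A reader might infer two hamlets per arm from the first draws. The draw continues until no names are left and the final number is not given, so two per arm is only a scenario.
- A reader might conclude that every interval is too narrow. Section 5.2 also compares baseline with follow-up. The children are largely the same ones: section 2.3 admits only those with a baseline evaluation, and Table 2 tracks attendance at all evaluations. Treating positively correlated measurements on one child as independent tends to overstate the standard error of change, which is the opposite direction.
- A reader might add the sentence "The chi-square test will be used to compare proportions" to the list of arm comparisons. It belongs to the baseline assessment and precedes the line that opens the arm comparisons.
- The relative risk is a usable point estimate. The problem lies in an unadjusted interval or test around it.

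**Conclusion.** The point holds for the between-arm comparisons. The analysis as written does not match the unit of randomisation, and this is more than missing detail. For any positive intra-hamlet correlation the direction is certain: standard errors and p-values too small, confidence intervals too narrow. The article's own account of where anemia occurs makes a zero correlation implausible for prevalence.

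The size is conditional. With 50 to 150 children per hamlet and an ICC of 0.01 to 0.05, both assumed, the design effect is 1.49 to 8.45 and the true type I error 11% to 50%. With at least 50 children per hamlet, the error rate at least doubles even at an ICC of 0.01. Confidence is high that no cluster adjustment is described, and lower about how large the error will be. The text should be corrected before any between-arm analysis is run.

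**What to change.** Rewrite the between-arm part of section 5.2 so that inference respects the hamlet. Either route will do:

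1. Compare baseline-adjusted hamlet-level means (hemoglobin) or proportions (anemia), with degrees of freedom from the number of hamlets. Residual variance may be pooled over the three arms.
2. Fit mixed models with random effects for hamlet and for child (repeated waves) and small-sample degrees of freedom. With at most 15 hamlets, uncorrected GEE or robust errors would still be too liberal.

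Give relative risks cluster-adjusted intervals, and report the ICC for each primary outcome. Say how within-child correlation is handled in the baseline-to-follow-up comparisons.

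State the number of hamlets that pass the daily-care screen. If it is small, for example six with two per arm, describe the results as exploratory and make no significance claim from child-level tests.

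The cost is analysis wording only. Hamlet identifiers should already be available from recruitment by hamlet and the surveillance system's household identification. The downside is wider intervals.

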### 2.3. Participants

All under-4 children and their mothers/caretakers, resident in the selected hamlets, will be considered eligible and invited to participate. This age group was selected because children are expected to have limited mobility, to receive higher parental attention and to have their exposure to contaminated environments more controllable than school aged children. Children will be subject to exclusion whenever having recently received blood transfusions, report adverse reactions to albendazole and/or to praziquantel, and when their caretakers do not commit to completing both the evaluation and the educational moments of the study. Only children with pre-intervention evaluation will be allocated to the Randomized Controlled Trial (RCT).

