## 4. Data Collection

### Educational Interventions

Caretakers participating in the intervention arms will have a monitoring file (consisting of six structured questionnaires (one for each monthly visit), applied by the technician to document behavioral alterations at every counselling visit and to record attendance to the community group sessions. Those educational interventions will be intercalated with cross-sectional evaluations. Those moments will have the same design as the baseline assessment, occurring respectively six and twelve months after the beginning of the study.

Data on the primary and secondary outcomes, which will be collected only in the follow up moments, aim at evaluating the impact of interventions. Considering that interventions are expected to influence either health and behavioral aspects, impact indicators are expected to provide information on changes in their frequency, and potential associations. On the other hand, data on the process indicators, which will be collected throughout the study, aim at assisting the evaluation of the quality and success of intervention’s delivery process. Thus, data regarding the provision, utilization and coverage aspects of the delivery process are expected to facilitate attributing the changes in primary and secondary outcomes to the intervention, by demonstrating that the intervention was of sufficient magnitude and occurred in a temporal sequence. Specifically, (1) provision indicators are expected to inform about the quality of provider’s training and performance, and if the requirements for provider’s optimal performance was delivered to them; (2) utilization indicators are expected to inform about the quality of receiver’s sensibilization, their receptivity to interventional activities, acquired knowledge and alterations of inadequate behaviors toward children; and (3) coverage indicators aim at providing information regarding the quality of the interventional activities, such as the adherence to them.

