1. Primary outcomes 1.1 Impact on health - Variation of hemoglobin levels; - Anemia prevalence reduction. 2. Secondary outcomes 2.1 Impact on Health - Iron deficiency anaemia reduction; - Micronutrient deficiencies (iron, folate, vitamins A and B12, zinc and vitamin E serum levels); - Prevalence reduction, intensity, incidence and reinfections rates of STH, *P. falciparum* and *S. haematobium*; - Prevalence reduction of Stunting (height-for-age) and wasting (weight-for-height). 2.2 Impact on Behavior - Exclusive breastfeeding (0–5 months) and continued breastfeeding (12–15 months) [68]; - Increase of Minimum dietary diversity prevalence (6–23 months) [68]; - Increase of Minimum Meal Frequency prevalence [68]; - Increase of iron and vitamin A rich foods consumption; - Reduction of morbidity from diarrhea (reported).	1. Acquired knowledge - Theoretical test scores (evaluation of knowledge); - Practical test scores (evaluation of counseling performance); - Self-counseling efficacy evaluation. 2. Counseling performance - Number of families dropping outs from evaluation moments per technician; - Number of families successfully visited for counseling by each technician; - Number of notified participants present in each community groups per technician; - Number of scheduled visits held successfully per technician.	1. Acquired knowledge of receivers -Theoretical test scores; - Practical test scores (participation in community groups); - Self-evaluation at mother-to-child care. 2. Participatory level of receivers (adherence) - N° of attendances to evaluation moments; - N° of scheduled visits (both in person and by telephone call) held successfully; - N° of scheduled visits that had to be redials due to absence or unavailability; - Mood state of the receiver between visits; - N° of attendances to communitarian group. 3. Household environment evaluation (observation) - N° of household hand washing mechanisms; - N° of communitarian latrines around the house; - Cleaning conditions classification of household latrines (if existent); - Cleaning conditions classification of the backyard; - Presence of pets loose in the yard and stool. 4. Mother-to-children care practices - Children using bednets; - Children sidewalks; - Children with clean nails.	1. Services provided at evaluation moments - N° of hospital-based consultation held for parasite treatment; - N° of domiciliary-based consultation held for parasite treatment; - N° of hospital-based consultation held for sickle-cell follow up; - N° of children referred to the emergencies with severe anemia, severe malnutrition and non-malarial fever who reported to have been followed. 2.Participatory level of receivers (adherence) - Proportion of child-caretaker pair present in all evaluation moments; - Proportion of child-caretaker pair presenting in all counseling moments; - Proportion of caretakers participating in all community groups; - N° of notified child-mother pair failing the hospital-based consultations for parasite treatment or sickle-cell follow up; - N° of child-mother pair failing to picking up the sickle-cell drugs.

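### The relative risk planned in section 5.2 is for cumulative incidence of anemia, but the binary primary outcome is anemia prevalence; the two can diverge in either direction

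*Protocol article*

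**What the plan says.** The between-arm analysis is in section 5.2 of the protocol article, under the unnumbered line on pre- and post-intervention and between-arm evaluations. It gives a general rule, "Outcomes will be compared analyzing for variance in the continuous variables and logistical regression for the categorical variables", and then adds one measure specific to anemia: "Relative risk will be calculated in order to compare the cumulative incidence of anemia among the intervention and control arms". It does not say which children are at risk or what counts as an incident case.

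The outcomes are in Table 2. The two primary ones are "Variation of hemoglobin levels" and "Anemia prevalence reduction". Incidence appears in that table only for the infections, where it is listed separately from prevalence, intensity and reinfection.

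On who enters, section 2.3 says: "All under-4 children and their mothers/caretakers, resident in the selected hamlets, will be considered eligible and invited to participate". None of its exclusions concerns anemia status, and it requires a pre-intervention evaluation before a child joins the trial. Section 1 cites regional studies that "reported a 57% prevalence of anemia in under-5 children". Section 4 calls the assessments cross-sectional ("Those educational interventions will be intercalated with cross-sectional evaluations") and times the two follow-ups as "occurring respectively six and twelve months after the beginning of the study".

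**The concern.** Prevalence at follow-up reflects two flows: non-anemic children becoming anemic, and anemic children recovering. Cumulative incidence reflects only the first, and it is defined only for children who start free of the condition. In a population where more than half may be anemic at entry, that removes the group in which recovery could be seen. If the denominator is instead all children, a child who was anemic at baseline and still is at follow-up is counted as a new case.

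The only between-arm effect measure that section 5.2 names for anemia therefore answers a different question from the outcome in Table 2. Because the at-risk group is not stated, the choice between the two denominators could also be made after the data are seen. The comparison between the two education packages, the third question in section 1.2, could be distorted too if one package works mainly through recovery and the other mainly through prevention.

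**Working it through.** The article gives no relative risk, event count or sample size, so there is no figure of its own to reproduce. The check asks how far the two measures can differ.

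**Inputs**
- Baseline prevalence 57% (section 1; earlier regional data in under-5s, not this trial's under-4 baseline).
- Assessments at 0, 6 and 12 months (section 4), hence two six-month intervals.
- Assumed, not in the article: control onset i = 30% and recovery r = 30% per interval.

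**At-risk share.** 1 − 0.57 = 0.43, so about 43 of every 100 children could contribute a first observed anemia.

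**Formulas**
- Prevalence after one interval: p′ = p(1 − r) + (1 − p)i, applied twice.
- Cumulative incidence by visit in children non-anemic at baseline: 1 − (1 − i)².

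**Control**
- 6 months: 0.57 × 0.70 + 0.43 × 0.30 = 0.528.
- 12 months: 0.528 × 0.70 + 0.472 × 0.30 = 0.511.
- Cumulative incidence: 1 − 0.70² = 0.51.

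**(a) Intervention raises recovery to 45%, onset unchanged**
- 6 months: 0.57 × 0.55 + 0.43 × 0.30 = 0.4425.
- 12 months: 0.4425 × 0.55 + 0.5575 × 0.30 = 0.411.
- Prevalence ratio: 0.411 / 0.511 = 0.80.
- Cumulative-incidence ratio: 0.51 / 0.51 = 1.00.

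**(b) Intervention lowers onset to 20%, recovery unchanged**
- 6 months: 0.57 × 0.70 + 0.43 × 0.20 = 0.485.
- 12 months: 0.485 × 0.70 + 0.515 × 0.20 = 0.4425.
- Prevalence ratio: 0.4425 / 0.511 = 0.87.
- Cumulative-incidence ratio: (1 − 0.80²) / 0.51 = 0.36 / 0.51 = 0.71.

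**The all-children denominator.** Suppose a case is any child found anemic at 6 or 12 months, whatever the baseline status. The share never found anemic is 0.57 × r(1 − i) + 0.43 × (1 − i)².
- Control: 0.57 × 0.21 + 0.43 × 0.49 = 0.330, so 0.670 are cases.
- (a): 0.57 × 0.315 + 0.43 × 0.49 = 0.390, so 0.610 are cases; ratio 0.91, against a prevalence ratio of 0.80.
- (b): 0.57 × 0.24 + 0.43 × 0.64 = 0.412, so 0.588 are cases; ratio 0.88, against 0.87.

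**Sensitivity.** Control onset was varied over 20–40% with recovery 30%, and onset 30% was also paired with recovery 50%. The intervention either multiplied recovery by 1.5 or onset by 2/3.
- Recovery-only effects: prevalence ratios 0.75–0.83, with a cumulative-incidence ratio of 1.00 throughout.
- Onset-only effects: prevalence ratios 0.81–0.89, with cumulative-incidence ratios 0.69–0.72.

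**The case against.** The strongest reply is that the primary outcome already has an analysis. Logistic regression is stated for categorical outcomes and can be applied to anemia prevalence. The relative risk is one added sentence, and section 1.2 does speak of preventing anemia, to which new cases in initially non-anemic children are relevant. The term may also be loose wording for the proportion anemic at follow-up, in which case correcting the term would be enough.

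Much of this stands. The primary outcome is not left without an analysis, and an incidence measure has a place as a secondary result. Loose wording is possible, but Table 2 separates prevalence from incidence where it means both, and on that reading the sentence still needs correcting.

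Four stronger readings are tempting but not supported:

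- *That the relative risk is the trial's main result.* Section 5.2 does not rank it above the other comparisons.
- *That the logistic odds ratio overstates the effect.* For a common outcome it lies further from 1: at a control risk of 57%, a risk ratio of 0.80 means 45.6% anemic and an odds ratio of (0.456/0.544)/(0.57/0.43) = 0.63. The odds ratio is still a valid measure. It misleads only if read as a risk ratio, and the article does not say it will be.
- *That restricting to non-anemic children inflates the standard error by √(1/0.43) = 1.52.* That treats children as independent, whereas hamlets are randomized. Assuming for illustration 100 children per hamlet and an intracluster correlation of 0.05, the design effects are 1 + 99 × 0.05 = 5.95 and 1 + 42 × 0.05 = 3.10, and the factor is √[(3.10/43)/(5.95/100)] = 1.10. It would also compare two different quantities.
- *That six-monthly assessment is itself the error.* Visit-based incidence would undercount episodes, but a 12-month prevalence does not see those between visits either.

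**Conclusion.** The point holds as a mismatch between a stated measure and a stated outcome. As written, the relative risk in section 5.2 does not estimate the reduction in anemia prevalence named in Table 2, and its denominator is undefined.

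Under the illustrated rates, a 20% relative reduction in prevalence could appear as no effect, and a 13% reduction as 29%. These sizes rest on assumed onset and recovery rates and on a regional prevalence that may not match the trial's own baseline. The direction does not depend on the exact figures: wherever many children are anemic at entry, an effect through recovery is invisible to an incidence ratio, and an effect through prevention looks larger in it than in prevalence.

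**What to change.** In section 5.2, replace the cumulative-incidence sentence with the between-arm risk ratio and risk difference for anemia prevalence at 12 months. Base them on all children with a baseline evaluation, adjust for baseline anemia status, and use inference that respects the randomized hamlets. A log-link model, standardized risks from the logistic model already planned, or a comparison of hamlet-level proportions would each serve.

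Report as secondary results, under those names, new anemia among children non-anemic at baseline and recovery among children anemic at baseline. Label any odds ratio from the logistic model as an odds ratio and do not describe it as a change in risk.

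The cost is analysis wording only. Baseline status is already required for every trial child by section 2.3, so no data collection changes. The wording should be settled before outcomes are compared by arm.
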